#### General information

The participants’ characteristics such as date of birth, gender, medical diagnosis, functional mobility scale (FMS) score and type and frequency of sport activity will be identified by a general questionnaire. An exercise pre-participation screening questionnaire will inquire about possible factors influencing the outcomes of the test and the participants’ safety during the tests. These questionnaires will take approximately 5 min to be filled out by the participant and/or parent.

#### Cardiovascular health

Cardiovascular health is divided in several aspects in this study: fat free mass, body mass index, arterial stiffness and blood pressure.

*Fat free mass* will be determined with bioelectrical impedance analysis (BIA), using the Bodystat Quadscan 4000 (EuroMedix, Leuven, Belgium). BIA is a non-invasive easy test to measure lean body mass and fat by comparing conductivity and resistance in the body (Mok et al. 2006). *Body mass index* will be calculated as weight (kg)/height (m)^2^. Weight will be measured using a wheelchair scale in case of subjects who are in the wheelchair group. In other cases a person weighing scale will be used. Height will be measured standing in case of ambulant subjects and supine in case of wheelchair bound persons. In case of spasticity, arm span width will be measured. Arm span length will be measured to the nearest centimetre from middle fingertip to fingertip. Body mass index (BMI) will then be calculated as the body mass divided by the square of arm span length that will be adjusted using arm span ×0.95 for mid‐lumbar lesions and arm span ×0.90 for high lumbar/thoracic lesions in case of central neurological disorders (Dosa et al. 2009).

*Arterial stiffness* has two independent measurement values: augmentation index: (AIX) and pulse wave velocity (PWV). Measurement will take place with the Arteriograph (Arteriograph.nl/LITRA, Amsterdam, the Netherlands). The Arteriograph measures the PWV and the AIX through the brachioradial artery using oscillometric tonometry. Each subject rests supine for at least 10 min before recordings are made. The measurement will take place with an inflatable cuff (similar to blood pressure measurement) at the right upper arm. Instructions to the subject are no food intake 3 h before measurement and no talking during the measurement. *Blood pressure* will also be measured using the Arteriograph within the same measurement.

After the pulse wave velocity measurement, the child is allowed to eat something, before continuing with the rest of the tests.

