## Design

The HAYS study will be a cross-sectional study comparing children and adolescents with a physical disability or chronic disease, age 10–19 years, who are actively participating in organized sports to their non-sporting peers. The subjects who participate in sports will be matched on gender, age and diagnosis to their non-sporting peers, Fig. 2.

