### Participants

Eligible for this study are all children and adolescents aged from 10 up to 19 years with a physical chronic disease or condition, including cardiovascular, pulmonary, musculoskeletal, metabolic or neuromuscular disorders. Table 1 shows the in- and exclusion criteria. Both children who are ambulatory or those propelling a wheelchair are eligible for this study. Participants have to understand the Dutch language, understand simple instructions and be able to perform a physical fitness test. Children and adolescents in electric wheelchair, having a progressive disease or participate in other research projects which might influence the current study results will be excluded. Contra-indications for performing an exercise test, based on the exercise pre-participation screening questionnaire, may lead to exclusion on the cardiopulmonary exercise test (Balady et al. 1998).

**Table 1 Tab1:** Eligibility and exclusion criteria

Eligibility	Exclusion
Children and adolescents with a physical disability or chronic disease: cardiovascular, pulmonary, musculoskeletal or neuromuscular disorder Children and adolescents between the age of 10 and 19 years Children and adolescents have to understand simple instructions Children and adolescents are able to perform physical fitness tests	Children and adolescents with progressive diseases Children and adolescents using an electric wheelchair During the length of the study, children are not allowed to participate in other research projects which might influence the current study results For the sporting group of the HAYS-study only: subjects who have not participated in any sports for the preceding 3 months No signed informed consent

Informed consent must be provided by all parents, as well as by subjects up from 12 years till 17 years. In line with Dutch law, no parental informed consent is required for subjects aged 18 years and over.

This study was approved by the Medical Ethics Committee of the University Medical Center Utrecht, the Netherlands.

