### Statistical analysis

Data will be checked for normal distribution before applying the right type of parametric or non-parametric tests. First, descriptive statistics will be used to describe the two samples. Independent sample T-tests or appropriate non-parametric tests will be used to to determine the differences between the sport and non-sport group.

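### Raw BMI is compared over ages 10–19 by an unpaired, unadjusted test, so growth-related spread stays in the standard error; the main harm is avoidable noise, not bias

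*Protocol article*

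**What the plan says.** The Cardiovascular health section divides this domain into "fat free mass, body mass index, arterial stiffness and blood pressure". It states that BMI "will be calculated as weight (kg)/height (m", squared). For children with spasticity, "Body mass index (BMI) will then be calculated as the body mass divided by the square of arm span length", with lesion-specific correction factors. Wheelchair users are measured supine. Table 3 lists the variable simply as BMI. No standard deviation score, percentile or growth reference appears in the article.

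Table 1 admits "Children and adolescents between the age of 10 and 19 years". The Design section says "The subjects who participate in sports will be matched on gender, age and diagnosis to their non-sporting peers", without stating how close in age a match must be. The Statistical analysis section applies one rule to all outcomes: "Independent sample T-tests or appropriate non-parametric tests will be used to to determine the differences between the sport and non-sport group". It mentions no pairing and no adjustment for age or sex. Date of birth and gender are recorded in the general questionnaire.

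**The concern.** BMI rises with normal growth, so the same kg/m² value describes a different weight status at 10 and at 19. Pooling this age range in an unpaired test puts growth into the error term. The matching could take it out, but the stated test ignores the matching.

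At stake are the width of the confidence interval and the power for one of the four cardiovascular outcomes. Because the study sets out to find negative as well as positive effects of sport, an interval wider than necessary makes a null result harder to interpret. If the age match turned out to be loose, part of the group difference would also reflect age. Blood pressure and pulse wave velocity get the same unadjusted comparison over the same ages.

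**Working it through.** **The plan's own figure.** The article gives no figure for BMI. Its sample size, 66 per group, is based on peak oxygen uptake. The stated inputs (difference 4.2, SD 8.2, two-sided alpha 0.05, power 0.80) give 60 per group by the normal approximation and 61 by the t-test. That discrepancy is a separate matter. Here 66 is only the group size.

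**Inputs.**
- Age range 10–19 (article). Uniform ages are assumed, so the age variance is 9²/12 = 6.75 and the age SD is 2.60 years.
- Rise in BMI with age: assumed 0.40, 0.55 or 0.65 kg/m² per year.
- Within-age SD of BMI: assumed 2.5, 3.0 or 3.5 kg/m².

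**Step 1: share of variance due to age.** Share = slope² × 6.75 / (slope² × 6.75 + SD²). Variance inflation = 1/(1 − share).

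| Slope | Age variance | SD 2.5 | SD 3.0 | SD 3.5 |
|---|---|---|---|---|
| 0.40 | 1.08 | 15%, 1.17 | 11%, 1.12 | 8%, 1.09 |
| 0.55 | 2.04 | 25%, 1.33 | 18%, 1.23 | 14%, 1.17 |
| 0.65 | 2.85 | 31%, 1.46 | 24%, 1.32 | 19%, 1.23 |

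The standard error used by the test is too large by the square root of the inflation: √1.09 = 1.04 to √1.46 = 1.21.

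**Step 2: power at middle values (slope 0.5, SD 3.0).** The age variance is 0.25 × 6.75 = 1.69, the share is 1.69/10.69 = 16%, and the total SD is √10.69 = 3.27. With age removed, the difference detectable with 80% power at 66 per group is (1.960 + 0.842) × 3.0 × √(2/66) = 1.46 kg/m². With the raw SD it is 1.59 kg/m². A true difference of 1.46 then has about 73% power in an unpaired comparison of unmatched groups.

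**Step 3: the same case under the matched design.** This used 20,000 simulated studies of 66 pairs, ages uniform on 10–19, with partners within half a year of each other (an assumed tolerance).

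| Analysis of raw BMI | Type I error | Power at 1.46 kg/m² |
|---|---|---|
| Independent t-test | 3.2% | 74% |
| Paired t-test | 4.9% | 79% |

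The mean difference with no true effect was 0.007 kg/m², which is effectively zero. With exact age matching and SD 3.0, the type I error of the independent test was 4.3% at slope 0.3 and 2.2% at slope 0.7. The test errs on the conservative side, more so as the slope gets steeper.

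**Step 4: bias if matching is loose.** Each year of difference in mean age shifts the BMI difference by the slope, 0.4–0.65 kg/m² under the assumptions. Without any matching, chance alone would give a difference in mean age with standard error 2.60 × √(2/66) = 0.45 years. A one-year gap would be about 2.2 standard errors, and matching makes it less likely.

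**The case against.** The strongest reply is that this is brevity rather than a choice. Weight over height squared is also the input to any standard deviation score, and the statistical section is three sentences for all outcomes. A full protocol or analysis plan, not shown, may name a reference. This stands in part: such a document could settle the point. But the article does state both a definition of the outcome and a test, and together they give an unadjusted comparison of raw BMI.

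The second reply is that the unpaired test is the real cause, that it affects every outcome that changes with age, and that a paired or adjusted analysis would recover most of the precision without a growth reference. This is correct, and it is why adjustment is offered below as an equal alternative.

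Three stronger readings are tempting, and the article does not support them:
- **That the comparison is biased.** The groups are to be matched on gender and age, the same variables that a standardised score would use. Bias requires that matching to be loose or incomplete. The article states no tolerance, but nothing in it shows a mismatch.
- **That a raw difference cannot be read as more or less overweight.** Between groups matched on age and sex, a higher mean BMI does mean heavier for height at comparable ages. Only its size is harder to interpret across the age range.
- **That standardising is free.** It needs no new data, but a growth reference may fit poorly where height is taken supine or replaced by corrected arm span.

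**Conclusion.** The point holds as one of avoidable noise. As written, the test leaves age-related spread in the standard error of the BMI comparison. Under the assumed slopes and SDs that spread is about 8–31% of raw variance, and at middle values the power loss is modest, from roughly 79% to 74%. The upper end pairs the steepest slope with the smallest SD and should not be taken as typical. Bias is conditional on a loose age match.

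The size rests wholly on assumed BMI slopes and SDs, uniform ages, and 66 per group. The simulation covers age only, not sex or diagnosis. Blood pressure and pulse wave velocity raise the same issue in principle, but no size is claimed for them. The sample size, which rests on peak oxygen uptake, is not touched.

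**What to change.** State in the Statistical analysis section one of the following:

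1. BMI is analysed as an age- and sex-specific standard deviation score from one named growth reference, with raw BMI reported as description.
2. Raw BMI is compared between groups in a model that adjusts for age and sex.

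Compare blood pressure and pulse wave velocity with the same adjustment for age and sex. Either BMI option removes most of the noise and also protects against an imperfect age match.

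If the score is chosen, add a check for children measured supine or by arm span: repeat the BMI comparison without them, or report the age- and sex-adjusted raw BMI alongside. The second check avoids the reference but keeps the mixed height measurements.

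The cost is a sentence or two and a lookup, since date of birth, gender, height and weight are already recorded. The drawback is the poorer fit of a reference for some children, which the check addresses.

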#### Physical fitness

Physical fitness consists of a combination of aerobic fitness, anaerobic fitness, muscle strength, flexibility and agility. Using the FMS for 500 meters the group of subjects will be divided in two sets depending on their mode of locomotion on this distance: wheelchair users and subjects who are able to walk with or without mobility aids. For these two groups, different testing tools will be used, appropriate for the type of locomotion.

Subsequently, within the group of subjects who are ambulatory different levels of mobility can be identified in order to apply a proper testing protocol, see Table 4.

**Table 4 Tab4:** Level of mobility for identifying testing protocol

Category	Level of mobility
I	Subjects with a very low level of mobility (able to walk <400 m in 6 min)
II	Subjects with a low level of mobility (able to walk > 400 m in 6 min)
III	Subjects with average level of mobility: walking indoors and outdoors and climbing stairs without limitations and able to perform gross motor skills including running and jumping
IV	Subjects with an excellent level of mobility, who are used to run at a speed of 8 km/h during their practicing their sports or during competition

#### Aerobic fitness

In exercise testing peak, oxygen uptake (VO_2peak_) is considered to be the single best indicator of the cardio-respiratory system, often referred to as aerobic fitness. A cardio-pulmonary exercise testing system, the Cortex Metamax 3X (Samcon bvba, Melle, Belgium), will be used for evaluating the respiratory gasses and VO_2peak_.

Bhambani et al. concluded that maximal exercise testing during the main mode of ambulation elicits the highest oxygen uptake. Therefore the type of sports or daily locomotion determines whether the shuttle run, shuttle ride or a cycling test will be used (Bhambhani et al. 1992).

Children who are able to walk will be tested with an (adapted) shuttle run test (Léger and Lambert 1982; Verschuren et al. 2006). The speed of the shuttle run test will be adjusted based on the results of the muscle power sprint test and the agility test and the level of mobility, see Table 4.

In children with a congenital cardiopulmonary disease a cycling test will be used, because of the monitoring of the heart for safety issues. The cycling test, using the Godfrey protocol (Washington et al. 1994), will also be applied to evaluate the aerobic fitness in children who are active on a bike in sports or daily living. Load depends on height of the child and the expected level of fitness.

A shuttle ride test will be used in children using a wheelchair. Shuttle tests are field tests in which a participant walks or runs between 2 markers. In this case they have to ride a distance of 10 meters in their own wheelchair, if applicable their sports wheelchair, between two cones. The starting speed is 2.0 km/h and the speed is increased with 0.25 km/h every minute. The children have to keep on riding, until they fail to reach the cone two times in a row, despite encouragements. This protocol has been proven valid as a maximal exercise test in youth with CP and spina bifida (Verschuren et al. 2013; Bloemen et al. 2015).

Regardless of the testing modality, the test will start with a resting steady state measurement for 3 min. To reach a total exercise time of at least 6 (children) and 8 (adolescents) minutes the protocol will be adapted based on the expected level of fitness. This might be due to the subjects high competition level for example or extreme athletic physique but also when a very low fitness is expected. In case of the cycling test, an unloaded phase of 1 min will precede the exercise phase. Each test will be until volitional exhaustion. Usual emergency procedures are in place to ensure health and safety in the very unlikely event of an emergency.

#### Anaerobic fitness

The muscle power sprint test is used to measure anaerobic fitness (Verschuren et al. 2007, 2013). Subjects have to complete six 15-m runs at a maximum pace. The MPST is an intermittent sprint test, in which the child stops and starts at standardized intervals. For children who self-propel manual a wheelchair, the MPST has also been proven a reproducible test for measuring anaerobic fitness and agility in children and adolescents with CP and SB (Verschuren et al. 2010, 2013).

Power output will be calculated for each of the six sprints: power = weight × (distance)^2^/(time)^3^. Peak power will be defined as the highest calculated power, while mean power was defined as average power over the six sprints.

#### Strength

To test the strength of the subjects, tests from the Brockport fitness test are chosen (Vanhees et al. 2005).

The handgrip strength will be tested through the use of a hand held hydraulic dynamometer (HHD) as described by Beenakker et al. (2001). The subjects dominant hand will be tested.

To measure the functionality of hand, wrist, and arm the reverse curl is used (Winnick and Short 1999). The participant attempts to pick up a (0.5-kg) dumb-bell with the preferred arm while seated in a chair or wheelchair.

The seated push up test is designed to measure upper-body strength and endurance (Winnick and Short 1999). Participants attempt to perform a seated push-up and hold it for up to 20 s.

The standing Broad jump (only for the ambulatory group) will be used to evaluate the explosive strength of the lower limbs by measuring the distance jumped with two legs together from standing position (Deitz et al. 2007). In wheelchair dependent participants, the one stroke push will evaluate the explosive strength of the upper limbs by measuring the distance one can cover in a wheelchair by one push (Verschuren et al. 2013).

#### Flexibility

To measure upper-body flexibility, the modified Apley test will be applied. The participant attempts to reach back and touch with one hand the superior medial angle of the opposite scapula. The modified Thomas test is designed to assess the length of the participant’s hip flexor muscles (M. Iliopsoas and M. Rectus Femoris) (Winnick and Short 1999).

#### Agility

The 10 × 5 Meter Sprint Test will be used to measure agility (Verschuren et al. 2013). During this test, the child has to sprint (for ambulatory and wheelchair users as well) as fast as possible, 10 times, in between 2 lines that are 5 meter apart. There is no resting period, so the child/adolescent has to turn as fast as possible during this test. Time will be recorded using a stopwatch.

#### Physical activity

Accelerometry in combination with heart rate monitoring will be used to measure the type, duration, frequency and intensity of physical activity in daily life. The Activ8 (2 M Engineering Ltd. Valkenswaard) will measure the modality of physical activity. The Activ8 system is new and has been recently be validated in cooperation with the Erasmus Medial Centre’s rehabilitation department in Rotterdam ([name] et al. work in progress). Participants who are able to walk wear one small sensor on the dominant leg. Participants in a wheelchair have to wear 2 small sensors (chest, one wrist). Participants will wear these monitors during the tests and during 7 days in their own environment. Wearing the activity monitor will not alter the activity pattern of the participants; all activities in daily life and in sport can be performed. The Actiheart (Camntech), will be used to detect the intensity of physical activity (Brage et al. 2005). The Actiheart is a small device detecting the heart rate frequency via two electrode-stickers on the chest and has been used previously in children with Spina Bifida (De Groot et al. 2013). During the 1 week of wearing the activity monitor, the participant will also fill out an activity diary in order to interpret missing data of the activity monitor. The completion of the activity diary will only take approximately 5 min per day.

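### Activ8 sensors are assigned by ability to walk rather than by mode used in sport, so a walking child who plays wheelchair sport wears only a leg sensor during those sessions

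*Protocol article*

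**What the plan says.** The Physical activity section describes three sources worn or completed over seven days.

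- **Activ8, for type of activity:** "The Activ8 (2 M Engineering Ltd. Valkenswaard) will measure the modality of physical activity". Placement follows two labels: "Participants who are able to walk wear one small sensor on the dominant leg", and "Participants in a wheelchair have to wear 2 small sensors (chest, one wrist".
- **Actiheart, for intensity:** "The Actiheart (Camntech), will be used to detect the intensity of physical activity". It uses chest electrodes and its placement does not depend on the Activ8 labels.
- **Diary:** participants "fill out an activity diary in order to interpret missing data of the activity monitor". Table 3, however, lists the diary beside the Activ8 as an instrument for type of activity, without limiting it to gaps in the recording.

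Two other sections bear on the labels. Under Physical fitness: "Using the FMS for 500 meters the group of subjects will be divided in two sets depending on their mode of locomotion on this distance", the two sets being wheelchair users and those able to walk with or without aids. Under Aerobic fitness, "the type of sports or daily locomotion determines whether the shuttle run, shuttle ride or a cycling test will be used". The Discussion repeats that the test mode should imitate the child's sport. The general questionnaire already records the FMS score and the type and frequency of sport.

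**The concern.** The placement rule looks at how a child can move, not at how the child moves in sport. For the one-off exercise test the authors recognise that these can differ and let the sport decide. For the week of monitoring, which is meant to capture sport as well as daily life, they do not.

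The child who falls through is one who walks but plays a wheelchair sport. That child is seated, with the arms doing the work, and the only Activ8 is on the leg. Daily physical activity is one of the comparisons named in the Abstract, and higher activity in the sport group opens the hypothesis in the Discussion. The sessions at risk are those that put the child in the sport group, so the error is not shared evenly between the groups.

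**Working it through.** The article gives no figure on this point to reproduce. The check is first a comparison of sections, then an illustration of size.

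**Step 1. Which set-up does each kind of child get?**

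| Child | 500 m split (Physical fitness) | Activ8 set-up (Physical activity) | Fits the sport? |
|---|---|---|---|
| Walks, ambulatory sport | able to walk | leg | yes |
| Wheelchair over 500 m, wheelchair sport | wheelchair user | chest + wrist, if the labels follow the split | yes |
| Walks over 500 m, wheelchair sport | able to walk | leg | no |

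Only the third row is a problem. The 500 m split does not rescue that child, because the child walks that distance.

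**Step 2. What goes wrong in the data?** The article does not say how a leg-worn Activ8 scores propulsion. It does move the sensors to chest and wrist for wheelchair participants, which implies that the leg position is unsuited to it. The likely result is a recorded but wrong type of activity. Such data are not missing, so the diary use described under Physical activity would not reach them, while the use implied by Table 3 could.

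**Step 3. In which group?** The Abstract defines the sport group by organised sport twice a week or more, over at least three months. Wheelchair sport at that level places the child in the sport group. If that group is truly more active, losing its sport time shrinks the observed difference.

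**Step 4. Illustration of size.** From the article: 2 sessions a week (the minimum) and 66 per group. Assumed: 60-90 min per session, all of it missed; 420 min/week of other recorded activity; SD 150-200 min/week; 5-20% of the sport group affected.

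- Lost per affected child: 2 × 60 = 120 to 2 × 90 = 180 min/week.
- As a share of that child's true active time: 120/(420 + 120) = 22%; 180/(420 + 180) = 30%.
- Shift in the sport-group mean: 0.05 × 120 = 6 to 0.20 × 180 = 36 min/week.
- SE of the difference = SD × √(2/66): 150 → 26.1; 200 → 34.8 min/week.
- Bias/SE: 6/34.8 = 0.17 to 36/26.1 = 1.38.

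A looser version, in which 10-50% of affected children's active time is spent in propulsion and missed, lowers the group mean by 0.05 × 10% = 0.5% to 0.20 × 50% = 10%. With no such children enrolled the bias is zero.

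**The case against.** A reader might infer more than the article supports, in three ways.

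- **Children who push a wheelchair over longer distances also get only a leg sensor.** This does not hold. The 500 m split uses the same able-to-walk label as the sensor rule, so the natural reading makes distance wheelchair users part of the two-sensor group. They also fit the wheelchair label directly. They are not part of this point.
- **Propulsion is recorded as sitting.** This is a reasonable inference about the device, but the article does not state it.
- **Physical activity as a whole is undercounted.** This is too broad. The Actiheart still registers the effort, so intensity survives. What is exposed is Activ8 type and duration.

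Further objections carry some weight. Table 3 makes the diary an instrument for type of activity, so the authors may already intend to use it as proposed; but the Physical activity section ties it to missing data, and the two need reconciling. The sports wheelchair is mentioned only in the test for wheelchair users, and the Aerobic fitness section also says that children able to walk do the shuttle run, so the article does not show that walkers in wheelchair sport are enrolled. Nothing in Table 1 excludes them, though, and recruitment includes sports clubs.

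Finally, this is a condensed article, activity is not the outcome on which the study is sized, and sensor handling may be detailed elsewhere. That would answer a complaint about silence. Here the article states a rule, and following it as written gives poorer data for these children.

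**Conclusion.** The point stands for one subgroup: children who walk, including over 500 m, and play a wheelchair sport. For their sport sessions, Activ8 type and duration would probably be misclassified, and the error works against the study's own hypothesis. Enlarging the sample would not remove it. A child in the comparison group who plays wheelchair sport below the qualifying frequency could have a smaller error of the same kind, but the sessions that define exposure are affected only in the sport group.

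The size cannot be judged. The range of about 0.2 to 1.4 standard errors rests on assumed values for the share of children, session length, SD and complete loss of each session; its upper end combines the least favourable values. It shows that the effect could be negligible or could matter, not which. The case for acting is that the remedy is cheap and a sensor worn in the wrong place cannot be corrected after the week is over.

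**What to change.** Replace the placement rule with one based on the modes the child uses in the monitored week, taken from the FMS score and the type of sport in the general questionnaire. A walker who plays a wheelchair sport then wears the chest and wrist sensors in addition to the leg sensor.

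If extra sensors are not practical, reconcile the Physical activity section with Table 3: state that wheelchair sport entered in the diary is recoded as active, with the Actiheart trace used to confirm start and end. Apply the same rule in both groups, without sight of the group label. Report how many children were affected and how much time was recoded.

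The change is a sentence or two in the monitoring procedure. The cost is one or two extra sensors, of a type already in use, for a minority of children, or some analyst time. It needs no extra visit and no extra participants.
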